The PATHWAY Group MCT multicentre, single-blind, randomised controlled trial aims to evaluate the effectiveness and cost-effectiveness of group-based metacognitive therapy for CR patients with elevated anxiety and/or depressive symptoms.^5^ Details of the main trial study protocol are available elsewhere.^5^ In brief, participants were recruited from patients with heart disease and referred for CR, in five UK National Health Service (NHS) Trusts. Trial participants had to meet CR eligibility criteria, score 8 or more on either the anxiety and/or depression subscale of the Hospital Anxiety and Depression Scale (HADS), be aged 18 years old or more and able to read, understand and complete questionnaires in English. Patients who gave informed consent to participate in the trial completed baseline assessments and were randomised via telephone link to Manchester Clinical Trials Unit. Participants were allocated to the intervention/comparator arms in a 1:1 ratio via a minimisation algorithm (incorporating a random component) to maximise balance between the two arms on gender, HADS score and hospital site. Participants randomised to the intervention arm received 6 weekly sessions of group-based metacognitive therapy delivered by either CR professionals or research nurses. The intervention and control groups were both offered in the usual CR programme within their Trust. The primary outcome is severity of anxiety and depressive symptoms at 4-month follow-up measured by the HADS total score.^13^ Secondary outcomes are severity of anxiety/depression at 12-month follow-up, health status, severity of post-traumatic stress symptoms, strength of metacognitive beliefs and service use at 4-month and 12-month follow-up. The PATHWAY Group MCT trial is part of a wider NIHR (National Institute for Health Research) programme grant for applied research, which began in August 2014 and with an end date of February 2021.

The aim of the economic evaluation component of the PATHWAY Group MCT trial is to estimate the cost-effectiveness of the addition of MCT intervention to CR for patients with elevated anxiety and/or depression symptoms, in a UK setting from a health and social care perspective. This will consist of a within trial analysis using patient-level data collected during baseline and follow-up study time points, and an economic model synthesising data from the trial and wider literature.

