
Multiple imputations will be conducted in Stata V.15, using predictive mean matching and sequential chained equations. Regression models used to impute missing data will be based on key covariates associated with costs or health benefits. A long list of potential covariates was identified from a recent systematic review of economic evaluations in the population undergoing cardiac rehabilitation and the baseline data collected within this randomised controlled trial (see online supplementary material). Discussions with clinical experts in the team will be used to assess the relevance and logic of using these variables as covariates in our analysis. This approach will be supplemented with pooled descriptive analyses and regression analyses to identify the final set of covariates.^6^ A list of potential covariates is included in the online supplementary material.

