#### Primary analysis

Costs and health benefit for the primary and sensitivity analyses will be estimated from baseline to end of 12-month follow-up, to estimate the incremental cost-effectiveness of the addition of MCT intervention.

The primary measure of interest for the economic analysis is the incremental cost-effectiveness ratio (ICER). Rather than considering cost and health benefit separately, the ICER is a joint measure of both. It is calculated by dividing the difference in costs (net costs) by the difference in QALYs (net QALYs) between any two interventions. The ICER represents the additional cost of an intervention per additional QALY gained:

$$ICER=\frac{Cost_{MCTinterventionplususualcare}-Cost_{usualcare}}{QALYs_{MCTinterventionplususualcare}-QALYs_{usualcare}}$$

Note that if the intervention is cost saving and produces more QALYs when compared with usual care (ie, it falls in the South East quadrant of the cost-effectiveness plane), an ICER will not be presented as intervention is dominant in such a scenario. Likewise, if intervention is dominated (ICER lies in the North West quadrant of the cost-effectiveness plane) it will be described in this way rather than calculated and presented numerically.

Descriptive analysis and data manipulation will be conducted using SPSS V.25 and the main statistical analyses will be conducted in Stata V.15.

Regression analysis will be used to estimate the net costs and QALYs of MCT. Cost and QALY data may not be normally distributed. Graphical summaries and descriptive statistics will be used to assess the distribution of the pooled cost and QALY data and identify the appropriate regression models for the analysis (eg, generalised linear model with gamma, log distribution for costs). Key covariates will be included in the regression models to control for baseline factors that may influence costs or QALYs. The covariates for these analyses will be identified using the approach outlined for the multiple imputation described in the previous section.

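### The process for choosing covariates in the cost and QALY regressions does not guarantee adjustment for the minimisation factors, baseline utility or baseline cost

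*Protocol article*

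**What the plan says.** The Primary analysis section of the within-trial analysis commits to adjustment in general terms: "Key covariates will be included in the regression models to control for baseline factors that may influence costs or QALYs". It names no covariate and refers back for the choice: "The covariates for these analyses will be identified using the approach outlined for the multiple imputation described in the previous section".

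The Missing data section describes that approach in three steps:

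- **Candidates:** "A long list of potential covariates was identified from a recent systematic review of economic evaluations", together with the baseline data collected in the trial. The list is in the online supplement, and the article calls its entries potential covariates.
- **Expert review:** "Discussions with clinical experts in the team will be used to assess the relevance and logic of using these variables as covariates".
- **Data step:** "This approach will be supplemented with pooled descriptive analyses and regression analyses to identify the final set of covariates".

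The Introduction says that allocation used a minimisation algorithm "to maximise balance between the two arms on gender, HADS score and hospital site". The Missing data section shows that baseline cost and utility are collected, and singly imputed where missing, but does not say that they enter the outcome regressions. In Table 2, gender and baseline HADS appear only as subgroup variables.

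**The concern.** Two kinds of covariate are normally fixed before the outcome data are examined: those that shaped the allocation, and the baseline value of the outcome. Here both depend on a process whose last step is run on the trial data. According to the Within-trial analysis section, follow-up ended in February 2019 and the economic analysis starts in April 2020, so outcome data are complete when that step is taken.

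The chosen set determines the models behind the ICER, the 10 000 bootstrap pairs and the acceptability curve. No sensitivity analysis in Table 2 varies the covariate set, so nothing planned would show how far the result depends on it.

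The consequences differ by covariate:

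- **Minimisation factors.** They are balanced by design. If they are prognostic and left out, the model ignores that balance and overstates the standard error.
- **Baseline utility.** It is part of the QALY by arithmetic and is not itself a minimisation factor. If it is left out, a chance difference at baseline passes into net QALYs.
- **Baseline cost.** It covers the three months before entry and so is not part of the outcome, but it is a natural predictor of later cost. The article gives no figures from which to size its omission.

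**Working it through.** The plan gives no figure to reproduce here. The main check is textual: the sections quoted above state how the final set is reached, and none exempts any variable from that process. The arithmetic below only sizes what could happen.

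**Inputs from the article:** visits at 0, 4 and 12 months and the trapezium formula (Outcomes); n = 332 with 1:1 allocation, taken as 166 per arm; five NHS Trusts; £20 000 per QALY as one commonly reported threshold.

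**Assumptions, not in the article:** utility SD 0.20 to 0.30; equal correlation r between visits of 0.5 to 0.7; minimisation factors explaining 5% to 20% of outcome variance.

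**1. Weight of baseline utility.** The intervals are 4/12 and 8/12 of a year. The weights are (4/12)/2 = 1/6 for baseline, (4/12 + 8/12)/2 = 1/2 for 4 months and (8/12)/2 = 1/3 for 12 months. So QALY = U0/6 + U4/2 + U12/3.

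**2. Worst case: baseline utility left out of the QALY model.**

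- Slope of the QALY on U0 = 1/6 + r × (1/2 + 1/3), which is 0.583 at r = 0.5 and 0.750 at r = 0.7.
- SE of the baseline difference = SD × √(2/166), which is 0.022 at SD 0.20 and 0.033 at SD 0.30.
- Shift in net QALYs for a one-SE imbalance = slope × SE. The low end is 0.583 × 0.02195 = 0.0128 (× £20 000 = £256). The high end is 0.750 × 0.03293 = 0.0247 (× £20 000 = £494).
- QALY variance in units of SD² = Σw² + r(1 − Σw²), with Σw² = 1/36 + 1/4 + 1/9 = 0.389. This gives 0.694 at r = 0.5 and 0.817 at r = 0.7.
- R² of the QALY on U0 = slope²/variance: 0.340/0.694 = 0.49 and 0.5625/0.817 = 0.69.
- SE reduction from adjusting = 1 − √(1 − R²): 29% and 44%.

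**3. Minimisation factors left out.** With balance by design, the standard error is overstated by 1/√(1 − R²).

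| Variance explained | SE overstated by | Actual level of a nominal 5% test |
|---|---|---|
| 5% | 2.6% | 4.4% |
| 10% | 5.4% | 3.9% |
| 20% | 11.8% | 2.8% |

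**4. Would the pooled regressions drop these covariates?** The article states no selection threshold, so take a 5% F-test with 332 complete records and noncentrality n × R²/(1 − R²).

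- Baseline utility at R² = 0.49: power is effectively 1.
- At R² = 0.05: power is 0.99 for one covariate, 0.93 for five sites (4 df) and 0.89 for all three minimisation factors (6 df).
- At R² = 0.10: power is above 0.99 in all three cases.

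**The case against.** The strongest reply is that the worst case defeats itself. A baseline utility that explains 49% to 69% of QALY variance would almost surely be retained. It would be at risk only if it were nearly uninformative, and then little is lost by dropping it. The same logic applies, less strongly, to the minimisation factors. This stands, and it is why the figures in step 2 cannot be read as the expected effect.

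The imbalance formula in step 2 also assumes simple randomisation. Minimisation on HADS may already restrain imbalance in utility, since anxiety/depression is an EQ-5D domain. That too points to the figures being an upper case.

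A reader might infer that covariates are picked by exploratory regression alone. The article does not support that: the regressions supplement a literature review and expert judgement. Pooled most plausibly means both arms combined, which limits selection towards a favoured treatment effect. The article also clearly intends some baseline adjustment.

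Finally, the candidate list is in a supplement not seen here, and an article may leave a final covariate list to an analysis plan. This part does not dispose of the point. The article does more than stay silent: it states a rule for reaching the final set. Appearing on a list of potential covariates would not by itself fix a variable in the model.

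**Conclusion.** The point holds in a limited form. The stated process is partly data-driven and does not guarantee adjustment for gender, HADS score, hospital site, baseline utility or baseline cost.

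Two stronger conclusions are tempting and should not be drawn. The first is that net QALYs will be off by £256 to £494 per participant, or that precision will be 29% to 44% worse. Those figures apply only if baseline utility is left out, and they rest on assumed SDs and correlations. The second is that omitting a minimisation factor biases the estimate. It mainly makes the standard error too large, by about 3% to 12% if the factors explain an assumed 5% to 20% of variance, so inference is conservative. That site in particular drives costs or QALYs is also not shown: the article says only that the content of usual rehabilitation varies by site.

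What remains is an avoidable dependence of the primary models on a selection step. The change is worth making because it is nearly free and removes that dependence for the covariates that matter by design or by arithmetic.

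**What to change.** In the within-trial Primary analysis section, state that gender, baseline HADS and hospital site enter both the cost and the QALY regression, with baseline EQ-5D utility in the QALY model and baseline cost in the cost model, whatever the pooled regressions show. State in the Missing data section that the same variables enter the imputation model. Keep the existing long list, expert discussion and pooled analyses for additional covariates only.

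All the variables are already collected. With five sites, and HADS entered as one continuous term, the fixed set uses about seven degrees of freedom per model (4 + 1 + 1 for the minimisation factors and 1 for the baseline value) out of 332 participants.

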#### Handling uncertainty

The estimates of costs and health benefits from the regression analyses will be bootstrapped to simulate 10 000 pairs of incremental cost and QALY outcomes of the MCT intervention.^14^ This captures the relationship between costs and QALYs. The pairs of net costs and QALYs will be plotted on a cost effectiveness plane to illustrate the level of uncertainty in the data.

Each of the net QALY estimates from bootstrap simulation results can be revalued by multiplying it by a willingness to pay threshold. Using these revalued QALY estimates it is then possible to estimate the net benefit statistic (NB) for each pair of simulated net costs and net benefits as:

NB = (O × threshold) – C, where O = net outcome score and C = net cost.

This process will be repeated for the WTPT values of interest to generate a cost effectiveness acceptability curve.

Additional sensitivity analysis will be used to test the impact of the study design on the ICER and results of the cost-effectiveness acceptability analysis. This will include subgroup analysis to estimate the impact of heterogeneity across the population, and scenario analysis to estimate the impact of study design on the cost-effectiveness of intervention. A detailed description of the likely sensitivity analysis and rationale are described in table 2. Note that the sensitivity analysis is informed by data collected in the trial.

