### Within-trial analysis

The analysis will use individual patient-level service use and health benefit data from all participants recruited and allocated to a management arm in the PATHWAY Group MCT trial (n=332). The trial opened for recruitment in July 2015 and closed in January 2018, follow-up finished in February 2019. The economic analysis of trial data will begin in April 2020 and will complete by September 2020. The analysis will compare the addition of group-based MCT to usual CR versus usual CR alone (standard practice) for individuals with elevated symptoms of depression and/or anxiety. The study sample for the economic evaluation is all participants randomised to receive the group-based MCT plus usual CR, or usual CR only. In brief, participants were people eligible and offered (referred to) CR as per NHS trust protocol, with a HADS score of 8 or more on the anxiety and/or depression subscale. The intervention, usual care and participant inclusion and exclusion criteria are summarised and described in detail in the trial protocol.^5^ Usual CR (dependant on NHS site) includes varying degrees, psychological interventions to address distress such as relaxation, stress management and some cognitive challenging.

The time horizon of the within-trial primary cost-effectiveness analysis will be 12 months, to incorporate sufficient time for any impact of MCT on service use, subsequent costs and health benefit. This differs to the primary clinical effectiveness time horizon, which will be 4 months (note, a sensitivity analysis will look at cost-effectiveness at 4-month follow-up).^5^

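### The within-trial analysis makes no allowance for therapy-group clustering in the MCT arm; if participants are resampled individually and the within-group ICC is above 0, uncertainty is understated

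*Protocol article*

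**What the plan says.** The *Introduction* describes individual allocation: "Participants were allocated to the intervention/comparator arms in a 1:1 ratio via a minimisation algorithm". The algorithm seeks "balance between the two arms on gender, HADS score and hospital site"; therapy group is not among the factors. It then states: "Participants randomised to the intervention arm received 6 weekly sessions of group-based metacognitive therapy delivered by either CR professionals or research nurses". Usual care has no corresponding grouping for MCT, so the design is partially nested: clustered by therapy group in one arm only.

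Under *Primary analysis*, "Regression analysis will be used to estimate the net costs and QALYs of MCT". The model family is to be chosen from the pooled distributions, with a gamma GLM as the example for costs, and adjustment is for baseline factors. Under *Handling uncertainty*, "The estimates of costs and health benefits from the regression analyses will be bootstrapped" to produce 10 000 pairs. These feed the cost-effectiveness plane, the net-benefit statistic and the acceptability curve. The only dependence mentioned there is that between costs and QALYs.

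Group size appears twice, both times for costing. *Resource use and costs* uses the trial's average group size to derive a cost per session, and Table 2 adds a scenario with larger groups. The within-trial sections, Table 2 and the limitations in the *Discussion* mention no therapy-group term, random effect, cluster-robust variance or resampling of groups.

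**The concern.** Members of one therapy group share facilitators, peers and session timing, so their later utilities and service use may be correlated. Where that correlation is positive, the MCT-arm mean varies more from trial to trial than independent observations would suggest. A bootstrap that draws individuals breaks up the groups and loses the between-group component. Running 10 000 draws reduces only Monte Carlo error and does not bring that component back.

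The planned covariates cannot do the job. They are baseline variables, whereas a therapy group forms after randomisation. Even if hospital site enters the model, five Trusts cannot represent some 17 to 42 therapy groups (166/10 to 166/4).

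At stake are the spread of the cost-effectiveness plane and the probability of cost-effectiveness read from the curve, which are the main within-trial statements of uncertainty. A decision-maker would see a probability somewhat further from 50% than the data justify.

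**Working it through.** The article gives no group size, ICC, standard deviation or power calculation, so there is no figure of its own to reproduce. The check asks how much the omission could matter.

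**Inputs from the article:** 332 participants (*Within-trial analysis*) and 1:1 allocation (*Introduction*), so about 332/2 = 166 per arm.

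**Assumptions:** equal groups of m = 4 to 10, all 166 MCT participants in groups, within-group ICC of 0 to 0.10, and the same individual-level variance in both arms.

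**Formulae**
- Design effect in the MCT arm: DE = 1 + (m − 1) × ICC.
- True SE of the difference relative to the individual-level SE: R = √[(1/166 + DE/166) / (2/166)] = √[(1 + DE)/2].
- Acceptability probability p after allowing for clustering: Φ(z_p / R), using a normal approximation to net benefit.

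**One case in full (m = 8, ICC = 0.05):** DE = 1 + 7 × 0.05 = 1.35. R = √(2.35/2) = √1.175 = 1.084. For p = 0.90, z = 1.2816; 1.2816/1.084 = 1.182, and Φ(1.182) = 0.881.

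| m | ICC | DE | R | 0.90 becomes |
|---|---|---|---|---|
| any | 0 | 1.00 | 1.000 | 0.900 |
| 4 | 0.02 | 1.06 | 1.015 | 0.897 |
| 4 | 0.05 | 1.15 | 1.037 | 0.892 |
| 6 | 0.05 | 1.25 | 1.061 | 0.887 |
| 8 | 0.05 | 1.35 | 1.084 | 0.881 |
| 10 | 0.05 | 1.45 | 1.107 | 0.877 |
| 6 | 0.10 | 1.50 | 1.118 | 0.874 |
| 10 | 0.10 | 1.90 | 1.204 | 0.856 |

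At p = 0.50, z = 0, so the probability stays at 0.50 whatever R is. The distortion grows only as the curve moves away from 50%.

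**Simulation check** (1500 trials per setting, 400 resamples each, 166 per arm, outcome SD 1):

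| m | ICC | True SE | Resampling individuals | Resampling groups |
|---|---|---|---|---|
| 6 | 0 | 0.1089 | 0.1090 | 0.1083 |
| 6 | 0.05 | 0.1171 | 0.1092 | 0.1142 |
| 8 | 0.05 | 0.1189 | 0.1092 | 0.1164 |
| 10 | 0.10 | 0.1316 | 0.1091 | 0.1277 |

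Resampling individuals returns about 0.109 whatever the ICC. Resampling whole groups recovers most of the missing variance, though not quite all of it when there are few groups (17 at m = 10).

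**The case against.** The strongest objection is that the article never says participants are treated as independent. *Handling uncertainty* names neither the resampling unit nor the variance estimator, and *Primary analysis* leaves the model family open. The article is condensed, its covariate list sits in a supplement that is not shown, and an unseen analysis plan might deal with clustering. This stands in part: a reader might infer that the plan commits to independence, but that would be reading a statement into silence. It does not dispose of the point. The article presents itself as the plan for the economic evaluation and goes down to the imputation method, the software version, the number of draws and the net-benefit formula. A reader following it at that level of detail would have no instruction to keep the groups together.

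Three further inferences are tempting but not supported:
- That the results will certainly be overconfident. This needs an ICC above 0; at 0 nothing changes.
- That confidence intervals will undercover. The within-trial sections promise an ICER, a plane and an acceptability curve, not intervals for net cost or net QALY.
- That the ICER, the stated primary measure, is wrong. A larger standard error around the same estimates leaves it unchanged.

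The calculation also leans high. Table 2 anticipates that some people allocated to MCT will not attend. Under intention-to-treat they stay in the arm without sharing sessions, which dilutes the average clustering.

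**Conclusion.** The point holds in a limited form. The design is clustered in one arm, the analysis as described does not allow for it, and baseline covariates cannot replace a grouping formed after randomisation. If individuals are resampled and the ICC is positive, the direction of the error is known: too narrow a plane, and a curve too extreme away from 50%.

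The size is modest. With 166 per arm, groups of 4 to 10 and an ICC of 0 to 0.10, the true SE is 0% to about 20% larger than the individual-level SE. A probability of 0.90 falls by 0 to about 4 points. For an ICC up to 0.05 the fall is roughly 0 to 2 points; the largest shift needs groups of 10 and an ICC of 0.10 together. Group size and ICC are assumptions throughout.

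This should be fixed because the remedy is cheap and is best settled before results are seen. A shift of this size does not make it a defect that invalidates the evaluation.

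**What to change.** Add to *Handling uncertainty*, in substance:

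> Bootstrap samples will be stratified by arm. In the MCT arm whole therapy groups will be resampled; in the usual-care arm individuals will be resampled. The cost and QALY models will both be refitted on the same resample. MCT participants with no identifiable therapy group will be treated as clusters of size one. The number and size of groups and the within-group ICC for costs and QALYs will be reported.

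An alternative, stated in *Primary analysis*, is a therapy-group random effect in the MCT arm only, or cluster-robust variance with each usual-care participant as their own cluster. If this route is taken, the 10 000 pairs must be generated with that variance and the cost–QALY covariance. A robust standard error alone leaves an individual-level bootstrap unchanged.

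In *Missing data*, reflect therapy group in the MCT-arm imputation where feasible. Values imputed without it would weaken the correlation that the bootstrap is meant to preserve.

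The cost is some extra Stata code, slightly wider uncertainty and the recovery of group membership. The trial team recorded MCT attendance, so membership should be available for attenders. It may not be for people who never attended, hence the rule for clusters of size one. No new data collection is needed.
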